### Randomization and intervention

2.6

The randomization protocol will be designed by a member of the Sichuan TCM Evidenced-Based Medicine Center. They will generate 204 random numbers will using SAS 9.2 statistical software (SAS Institute, Cary, NC). Treatment allocation will be conducted by an independent statistician according to the random numbers generated by the statistical software. Eligible patients will be randomly assigned to either the TCM group or the placebo group using sealed opaque envelops after obtaining informed consent. A special manager will record this randomization process. An individual's randomization number and group allocation can be identified by checking the envelope, which will be performed in case of a clinical emergency.

All participants will receive basic Western medical therapy advocated by the Chinese Expert Consensus on the diagnosis and treatment of AECOPD (2017 update),^[8]^ which includes:

1.Controlled oxygen therapy: Venturi mask inhales oxygen.2.Bronchodilators: compound ipratropium bromide solution for inhalation (Laboratoire Unither, Amiens, France), 2.5 mL, inhale, three times a day;3.Phlegm medicine: fudosteine tablets (Pharmaceutical Co., Ltd.), 0.4 mg, orally, three times a day;4.Glucocorticoids: methylprednisolone sodium succinate for injection (Tianjing Jinyao Pharmaceutical Co., Ltd. Tianjing, China), 40 mg, administered with 0.9% sodium chloride injection (100 mL), intravenously, once a day (depending on the patient's condition, the dosage can be reduced or changed to oral administration, but the longest course of treatment cannot exceed 14 days);5.Antibacterial drugs: according to bacterial resistance and the general course of treatment will be 5 to 7 days, although special circumstances can appropriately extend the application time of antibacterial drugs.

In addition, the TCM group will receive TCM granules (one bag at a time, three times a day) and the Placebo group will receive Placebo granules (one bag at a time, three times a day). Both groups will or will not receive antibiotic treatment according to the antibiotic treatment criteria, which are:

1.During AECOPD, aggravated difficulty breathing, increased sputum volume, and purulent sputum occur simultaneously;2.The patient only has two of the above three symptoms, but has purulent sputum;3.Severe acute exacerbation that requires invasive or noninvasive mechanical ventilation.

**TCM granules.** The TCM granules will be provided by the Sichuan Green Pharmaceutical Technology Development Co., Ltd. (Sichuan, China). The main components of TCM are presented in Table 1.

**Table 1 T1:**
[figure not shown]
Main components of traditional Chinese medicine.

**Placebo.** The appearance and taste of the placebo, which consists of starch without any active ingredient, will be as close as possible to the TCM granules. The drug instructions for the placebo will be consistent with those for TCM granules and will be produced by the same manufacturer.

### Length of intervention time

2.7

The entire hospital stay will be ∼7 to 14 days.

### Discharge criteria

2.8

The theoretical discharge criteria will be^[8]^:

1.Clinicians believe that patients can adapt to home medical care;2.Patients can use long-acting bronchodilators, such as β2 receptor agonists and anticholinergics, with or without inhaled glucocorticoids for stable inhalation therapy. Inhaled short-acting β2 receptor agonists should be administered less than once every 4 h;3.If the patient is not bedridden, they need to be able to walk indoors;4.Patient is able to eat and sleep and is not affected by dyspnea;5.Patient clinically stable for 12 to 24 h;6.Arterial blood gas analysis is stable for 12 to 24 h;7.The patient (or family member) fully understands the proper use of the drug in the stable phase;8.Follow-up and care plans are properly arranged (e.g., follow-up to community doctors and family medicine).

### Follow up

2.9

Patients will be followed up by phone once a week for 12 weeks after discharge. The contents of the follow up mainly included the scores of CAT, mMRC, and 6MWD.

### Primary outcome measure

2.10

**The dosage of systemic glucocorticoids (at which the CAT scores improve by 50%)**. Measurement methods: ([admission CAT scores − post-intervention CAT scores)/admission CAT scores) × 100%. Record glucocorticoids dosage in case report form (CRF) based on CAT scores.

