### Trial design and oversight

2.1

This will be a prospective, placebo-controlled clinical trial to evaluate the efficacy of TCM in the treatment of patients with AECOPD. A total of 204 eligible patients will be enrolled according to the exclusion and inclusion criteria and randomly assigned to the TCM or placebo group at a 1:1 ratio. The antibiotic group and non-antibiotic group will be set in advance for subgroup analysis. After a 7–14 day intervention and 12 weeks of follow up, the efficacy of TCM in the treatment of patients with AECOPD will be evaluated based on the primary endpoint (the dosage of systemic glucocorticoids [at which CAT scores improve by 50%]) and secondary endpoints (symptoms scores, exercise tolerance, lung function, length of hospital stay, symptoms, and quality of life scores during the follow up). The flow chart of the study is presented in Figure 1.

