### Sample size

2.5

Based on the primary endpoint (the dosage of systemic glucocorticoids) to calculate sample size. According to a previous study,^[17]^ the dosage of systemic glucocorticoids during the hospitalization of patients with AECOPD with TCM is 187.6 ± 31.1 mg (methylprednisolone sodium succinate for injection) and that with western medicine treatment is 256.7 ± 32.9 mg. Using a formula, we will set α = 0.05 and β = 0.2 and hope that 80% power can be used to uncover the true difference between the treatment options. According to the formula, nc = (μ1−α / 2 + μ1−β) ^2^S^2^ (1 + 1 / k) / (μt-μc) 2 = 87. Thus, the control group requires 87 cases. According to the 1:1 ratio, a total of 174 cases are needed in the two groups. Considering a possible dropout rate of 15%, a total of 174/0.85 = 204 cases are required, with 102 cases in each group.

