### Statistical analysis

2.16

Intention-to-treat analysis and per-protocol analysis will be used. Intent-to-treat analysis means that after subjects are randomized, whether they choose to withdraw from the trial or switch to another group, their results are based on their initial grouping during data analysis. Intention-to-treat analysis will be used to analyze completed cases and dropout cases. Efficacy analysis adopts per-protocol analysis; thus, it kicks out those cases with insufficient compliance during the analysis and analyzes only the completed cases. When there is a difference between the two results, the difference will be discussed and explained.

We will use SPSS 19.0 statistical software for statistical analysis. The measured value of the data will be expressed as mean ± standard deviation. If the data follow the normal distribution and the variance is homogeneous, the *t* test will be used; however, if the data does not follow the normal distribution or the variance is uneven, the Wilcoxon rank-sum test will be sued. The Bonferroni method will be used to further compare the differences between antibiotic and non-antibiotic subgroups to explore whether antibiotics will affect the outcomes. The Chi-square test will be used for counting data and rank-sum test will be used for ranking data. All tests will be two-sided, with *P* < .05 being considered statistically significant.

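### The primary endpoint has no value for a randomised patient whose CAT score never improves by 50%, and the sample size rests on a different dose quantity

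*Protocol article*

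**What the plan says.** All references are to the protocol article.

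- **Section 2.10, Primary outcome measure:** the endpoint is "The dosage of systemic glucocorticoids (at which the CAT scores improve by 50" per cent). The formula given is the percentage change in CAT from admission to after the intervention. The recording instruction is "Record glucocorticoids dosage in case report form (CRF) based on CAT scores".
- **Section 2.1, Trial design and oversight:** the same condition appears, as "the primary endpoint (the dosage of systemic glucocorticoids [at which CAT scores improve by 50" per cent]).
- **Section 2.5, Sample size:** the calculation is said to rest on the primary endpoint, but the planning figures are "the dosage of systemic glucocorticoids during the hospitalization of patients with AECOPD with TCM", 187.6 ± 31.1 mg, while "that with western medicine treatment is 256.7 ± 32.9 mg". No CAT condition is attached.
- **Introduction and Discussion:** the primary endpoint is the steroid dose, or its reduction, again without the condition.
- **Section 2.16, Statistical analysis:** intention-to-treat by initial group, covering completers and dropouts, plus a per-protocol analysis of completed, compliant cases. Group means are compared by t test or rank-sum test.

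**The concern.** A dose at 50% improvement exists only for a patient who gets there. For anyone else the definition yields nothing, and the article names no substitute value. The intention-to-treat text deals with withdrawal and switching, not with a patient who stays in the trial and simply has no outcome.

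Whether a patient reaches 50% is decided after randomisation, and the granules are meant to influence it. If only patients with a value are compared, the two groups are no longer the groups that were randomised, and the estimated dose difference may be biased. Separately, a sample size computed on total in-hospital dose gives no assurance of power for dose at a symptom threshold.

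**Working it through.** **1. Can a patient lack a value?** Yes, on the document's own terms. The stay is about 7 to 14 days (Sections 2.7 and 2.14), the steroid course is capped at 14 days (Section 2.6), and none of the eight discharge criteria (Section 2.8) refers to CAT. A patient can therefore be discharged below 50% improvement.

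**2. The definitions side by side**

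| Place | Quantity | 50% CAT condition |
|---|---|---|
| Introduction | steroid dose | no |
| 2.1 | steroid dose at a CAT threshold | yes |
| 2.5 | steroid dose during hospitalisation | no |
| 2.10 | steroid dose at a CAT threshold | yes |
| Discussion | reduction in steroid dose | no |

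These are two different variables. Dose to the threshold cannot exceed total in-hospital dose, and it is lower whenever dosing continues past the threshold.

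**3. The plan's own figure.** Inputs from Section 2.5: difference 256.7 − 187.6 = 69.1 mg; S² = (31.1² + 32.9²)/2 = 1024.8; "α = 0.05 and β = 0.2"; k = 1. Section 2.16 adds "All tests will be two-sided". The printed formula gives

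n = (1.960 + 0.842)² × 1024.8 × 2 / 69.1² = 3.4, so 4 per group.

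The stated 87 is not reproduced; it would need an SD of about 163 mg or a difference of about 13.6 mg. That is a separate defect and nothing below depends on it. I use 87 only as the planned number per group.

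**4. Loss of numbers alone.** The standardised effect that 87 per group detects with 80% power is (1.960 + 0.842)/√(87/2) = 0.425. If a share r has a value and the effect is unchanged, power = Φ(0.425 × √(87r/2) − 1.96). The share r is an assumption.

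| r | Power | Evaluable patients per group needed to keep 87 with a value (87/r) |
|---|---|---|
| 0.9 | 76% | 97 |
| 0.8 | 71% | 109 |
| 0.7 | 65% | 125 |
| 0.6 | 58% | 145 |
| 0.5 | 51% | 174 |

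**5. Adding selection.** Assumptions: a constant 40 mg/day (the figure in Section 2.6), lognormal days to 50% improvement with log-SD 0.5, rounded up to whole days, and a cap at day 14. The all-patient dose is 40 × min(day of 50%, 14). The reacher analysis keeps only patients with day ≤ 14, so n = 87 × share reaching. Power = Φ(difference/SE − 1.96), with SE = √(SD₁²/n₁ + SD₂²/n₂).

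| Median days, control v TCM | Mean dose, all (mg) | Reach 50% | Difference, all v reachers (mg) | Power, all v reachers |
|---|---|---|---|---|
| 5.3 v 3.7 (set to the Section 2.5 means) | 256.7 v 187.6 | 97% v 99.6% | 69.1 v 62.4 | 99.4% v 99.0% |
| 10 v 8 | 412.9 v 356.4 | 75% v 87% | 56.5 v 38.1 | 81% v 51% |
| 14 v 11 | 485.6 v 435.6 | 50% v 68.5% | 50.0 v 32.8 | 82% v 34% |

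The last row in full. All patients: SE = √(104.4²/87 + 124.4²/87) = 17.4; 50.0/17.4 = 2.87; Φ(0.91) = 0.82. Reachers: SE = √(103.6²/43.5 + 110.5²/59.6) = 21.3; 32.8/21.3 = 1.54; Φ(−0.42) = 0.34.

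**6. Direction.** With the stay drawn uniformly from 7 to 14 days instead, medians of 10 v 7 days give 52% v 76% reaching, and a difference of 58 mg in all patients against 49 mg in reachers. Medians of 14 v 10 days give 29% v 52% reaching, and 38 mg against 41 mg. The reacher comparison can therefore understate or overstate the all-patient difference.

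**The case against.** The strongest reply is that this is a condensed article and an unseen analysis plan may say how non-reachers are scored. That is possible. It would not settle the matter, because the variable itself is fixed here in two incompatible ways, and Section 2.5 calls its quantity the primary endpoint.

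Several stronger readings are tempting but not supported:

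- **That the protocol plans a responders-only comparison.** It does not say so. Per-protocol exclusion in Section 2.16 is for poor compliance, not for missing a CAT target. The restriction is what happens if the gap is left unfilled.
- **That a single post-intervention CAT makes the threshold dose unmeasurable.** Section 2.11 has CAT scored daily in hospital, and Section 2.14 has both CAT and dose recorded daily, so the day of first 50% improvement can be found.
- **That power will collapse.** The large losses come from slow-response medians that imply mean doses of 356 to 486 mg, well above the 187.6 and 256.7 mg of Section 2.5. Set to those means, the same model shows almost no power loss. That calibration is also an assumption: it treats in-hospital dose as dose to 50%, and it matches the means but not the planning SDs.
- **That the result will reverse.** One can build a reversal: 60% of controls reach at a mean of 280 mg, and TCM has the same 60% plus 15% late reachers at 520 mg, giving (0.60 × 280 + 0.15 × 520)/0.75 = 328 mg. This shows possibility only.

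Section 2.6 says "the dosage can be reduced or changed to oral administration", and the article does not state how oral and intravenous milligrams are combined. That conversion is a detail commonly left to a fuller document, and so is any special ranking of deaths. Neither is part of this point.

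**Conclusion.** The point stands on two grounds in the text. First, Sections 2.1 and 2.10 define a primary endpoint that does not exist for a randomised patient who leaves hospital below 50% CAT improvement, so the intention-to-treat analysis of Section 2.16 cannot include that patient as things stand. Second, Section 2.5 sizes the trial on a different quantity.

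The size of the harm is unknown, because the protocol gives no expected share reaching 50%. The illustrations run from almost no loss of power (99.4% to 99.0%) to a large one (82% to 34%), and the bias can go either way. They rest on constant dosing, a lognormal response time and chosen medians. Their all-patient comparator stops counting dose at 50% improvement, so they test the rule that counts non-reachers at full dose, not total in-hospital dose. The definitional fault needs none of these assumptions.

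**What to change.** Reconcile the Introduction, Sections 2.1, 2.5 and 2.10 and the Discussion to one primary endpoint that has a value for every randomised patient. The preferred choice is cumulative systemic glucocorticoid dose from randomisation to discharge or day 14, whichever comes first. This matches the quantity in Section 2.5 and allows intention-to-treat as described.

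Keep dose to first 50% CAT improvement, taken from the daily CAT, as a secondary endpoint. Censor patients who do not reach 50% at their total dose instead of excluding them.

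If the 50% endpoint stays primary, count non-reachers at their full in-hospital dose, and state in Section 2.5 that the planning figures refer to a different quantity.

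The cost is a protocol amendment with ethics approval and a registry update. No new data are needed, since dose and CAT are already recorded daily. This concerns only how the outcome is defined and implies nothing about how steroids should be given.

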### Study procedures

2.14

Eligible subjects will be screened 2 days before the trial. Randomized group treatment will be conducted after informed consent is obtained and baseline information is collected. The duration of the intervention will be the entire hospital stay (7–14 days). All hospitalized patients will complete the CAT, mMRC, and 6MWD scales every day. The physician should record each patient's glucocorticoid dosage every day and make corresponding adjustments according to the CAT scores. The patients will be asked about their symptoms and quality of life scores (assessed by CAT, mMRC, and 6MWD) after discharge for 12 weeks by weekly telephone follow-up. The spirit figure of enrollments, interventions, and assessments is presented in Figure 2.^[15]^

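### The primary outcome is defined inconsistently: Section 2.10 scores a glucocorticoid dosage tied to 50% CAT improvement, with no rule for summing doses, while Section 2.5 sizes the trial on total milligrams over the hospital stay

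*Protocol article*

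**What the plan says.** Section 2.10 (Primary outcome measure) gives the outcome as "The dosage of systemic glucocorticoids (at which the CAT scores improve by 50" per cent. Section 2.1 repeats that definition. Under measurement methods, Section 2.10 has one formula, "admission CAT scores − post-intervention CAT scores)/admission CAT scores) × 100" per cent, and one instruction: "Record glucocorticoids dosage in case report form (CRF) based on CAT scores".

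Section 2.5 (Sample size) names the dosage of systemic glucocorticoids as the primary endpoint without the CAT condition, as the Introduction also does. Its planning value is that "the dosage of systemic glucocorticoids during the hospitalization of patients with AECOPD with TCM is 187.6 ± 31.1 mg", against 256.7 ± 32.9 mg with western medicine.

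Section 2.6 gives the regimen as "40 mg, administered with 0.9% sodium chloride injection (100 mL), intravenously, once a day" and adds that "the dosage can be reduced or changed to oral administration, but the longest course of treatment cannot exceed 14 days". Section 2.14 (Study procedures) says: "The physician should record each patient's glucocorticoid dosage every day and make corresponding adjustments according to the CAT scores". CAT is also scored every day in hospital (Sections 2.11 and 2.14).

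**The concern.** The word *dosage* carries two meanings. In Sections 2.6 and 2.14 it is a level that is given, recorded and adjusted day by day. In Section 2.5 it has to be an amount accumulated over days. Section 2.10, which should settle the matter, does not say which is scored, and its formula produces neither milligrams nor a day.

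The readings are different variables. A daily dose at the moment of recovery is not a measure of how much steroid a patient received. A cumulative dose up to 50% improvement and a total over the stay both measure exposure, but over different windows, and only the second is the quantity used for sizing. If those who complete the case report form and those who analyse it follow different readings, the primary result may be null, or may even change direction, for reasons unrelated to the treatment.

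**Working it through.** **1. The planning figures.** From Section 2.5: means 187.6 and 256.7 mg, difference 256.7 − 187.6 = 69.1 mg. From Section 2.6: 40 mg once a day, for at most 14 days.

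- 187.6 / 40 = 4.69 days of drug
- 256.7 / 40 = 6.42 days of drug
- longest course: 14 × 40 = 560 mg

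Set against this regimen, the planning figures are plausible only as accumulated amounts. Section 2.5 also describes them as covering the hospital stay.

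**2. The stated sample size.** The formula in Section 2.5, with pooled variance (31.1² + 32.9²)/2 = 1024.8, two-sided α = 0.05 and 80% power, gives (1.960 + 0.842)² × 1024.8 × 2 / 69.1² = 3.4, so 4 per arm. The plan states 87. That discrepancy is a separate matter. Nothing below depends on it, and it does not help to identify which quantity was meant.

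**3. What the Section 2.10 formula delivers.** It returns a percentage from one admission score and one post-intervention score. Section 2.14 makes the intervention last the whole stay, so a post-intervention score falls at its end. It can show whether 50% was reached by then, but not on which day. It therefore cannot locate the point at which a dosage is to be read.

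**4. The three readings, side by side.**

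| Reading | Fits Section 2.10? | Fits Section 2.5? |
|---|---|---|
| Daily dose when 50% is reached | Possible | No: wrong scale |
| Cumulative dose up to that day | Possible | Right scale, different window |
| Total over the stay | Only if the CAT condition is ignored | Yes |

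**5. The daily reading on the sizing scale.** If every daily dose lies between 0 and 40 mg, both arm means do too, so they differ by at most 40 mg, less than 69.1 mg.

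**6. How the daily reading behaves.** The schedules and milestone days here are assumptions for illustration, not rules in the protocol.

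- *No reduction before the milestone.* Every patient scores 40 mg, so the difference is 0, however much sooner one arm recovers.
- *Reductions that follow CAT.* If the day's dose depends on that day's CAT improvement, patients reaching 50% are on about the same dose in both arms, so the difference is near 0.
- *Reduction on a calendar day.* Assume 40 mg on days 1 to 5, then 20 mg. A patient reaching 50% on day 4 scores 40 mg after receiving 4 × 40 = 160 mg. A patient reaching it on day 7 scores 20 mg after receiving 5 × 40 + 2 × 20 = 240 mg.

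For arm means under the same calendar taper, assume normally distributed milestone days with means 4.7 and 6.4, SD 1, rounded to whole days:

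- faster arm: P(day ≤ 5) = Φ(5.5 − 4.7) = Φ(0.8) = 0.788, mean daily dose 20 + 20 × 0.788 = 35.8 mg
- slower arm: P(day ≤ 5) = Φ(5.5 − 6.4) = Φ(−0.9) = 0.184, mean daily dose 20 + 20 × 0.184 = 23.7 mg
- cumulative means to the milestone, by simulation of 100,000 patients per arm: 183 versus 227 mg

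The daily reading here favours the slower arm, while the cumulative reading favours the faster one.

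**The case against.** A reader might infer that the rule, taken literally, scores the daily dose, that this value is capped at 40 mg, and that a real benefit would be reported as harm. The document does not support that.

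- **Section 2.10 never says daily.** A cumulative amount at the point of 50% improvement fits the same words. Section 2.5 uses the same noun for an accumulated quantity, which suggests that the authors mean one. In Section 2.14, the daily wording describes when dosage is recorded.
- **40 mg is not an explicit ceiling.** Section 2.6 names only reduction or an oral switch, but Section 2.14 allows adjustments with no stated direction, and no oral drug or conversion is given. The scale mismatch does not need a strict ceiling, however: 256.7 mg is 6.4 times the only stated dose.
- **The reversal needs a calendar taper.** Section 2.14 ties adjustments to CAT, which points to a difference near zero instead.
- **The milestone days are constructed.** They come from dividing whole-stay totals by 40 and treating the result as time to 50% improvement, which the document never does.
- **This is a condensed article.** A derivation rule may well sit in a fuller protocol or analysis plan, so its absence alone would be no finding.

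All five points stand, and they limit the claim. They do not remove it. What remains is a conflict between sections that are printed: Section 2.10 attaches a CAT condition that Section 2.5 does not, and gives a formula that yields neither a dose nor a day.

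**Conclusion.** The concern holds as an inconsistent definition of the primary outcome. Three readings are open, and nothing in Section 2.10 chooses between them. The daily reading is incompatible with the sizing. This rests on 40 mg once a day being the only stated dose, under which 69.1 mg is unattainable. The cumulative-to-milestone reading has the right scale but not the window that Section 2.5 uses. Only the whole-stay total matches the sizing, and it leaves the CAT condition without a role.

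The effect on the trial's conclusion depends on how doses are changed in practice, which the document does not specify. Under the daily reading the difference would be zero without reductions and near zero if they follow CAT. It is reversed under the assumed day-5 taper (35.8 versus 23.7 mg, against 183 versus 227 mg cumulative). The reversal is a possibility, not a prediction. Because this is the primary outcome, the definition should be settled before any outcome data are compared.

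**What to change.** Reconcile the Introduction and Sections 2.1, 2.5, 2.10 and 2.14 on one quantity:

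1. State that the primary value is the cumulative milligrams of systemic glucocorticoid received, in one stated methylprednisolone-equivalent unit so that an oral switch can be added. Sum it in the analysis dataset from the daily dose records, not from a single dosage entered at a milestone.
2. Name one window.
   - **If it ends at 50% CAT improvement:** replace the post-intervention score in the formula with the CAT score on day t, take the first day that reaches 50%, and say how patients who never reach it are scored. Also state in Section 2.5 that the planning figures are whole-stay totals and so describe a different window.
   - **Otherwise:** drop the CAT condition from Sections 2.1 and 2.10 and use the whole-stay total, as Section 2.5 does.

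The cost is a protocol amendment, which Section 2.1 says needs renewed ethics approval, and a derivation that includes the unit conversion and, for the milestone window, the non-responder rule. Daily doses and daily CAT scores are already collected, so no new visits or patients are needed. No dose or titration rule has to change.

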### Inclusion criteria

2.3

Patients who meet the diagnosis of phlegm-heat congested lung syndrome of AECOPD and need systemic glucocorticoid administration;COPD GOLD stage 3 or 4 (post-bronchodilator forced FEV1/FVC < 70% and FEV1 < 50% of predicted);Age from 40 to 65 years old and have symptomatic COPD (CAT scores ≥ 10), regardless of sex;No history of allergies to the drugs used in the experiment;Expected survival time ≥30 days;Patients and their families agree to participate and sign informed consent.

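### The primary outcome is the steroid dose at a 50% CAT improvement, which patients who never reach that point do not have, while the sample size uses a dose that every patient has

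*Protocol article*

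**What the plan says.** Two sections of the protocol article define the primary outcome by a CAT milestone. Section 2.1 (Trial design and oversight) gives "the dosage of systemic glucocorticoids [at which CAT scores improve by 50" per cent. Section 2.10 (Primary outcome measure) gives "The dosage of systemic glucocorticoids (at which the CAT scores improve by 50" per cent, adds the formula for percentage change in CAT from admission, and instructs: "Record glucocorticoids dosage in case report form (CRF) based on CAT scores".

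Section 2.5 (Sample size) uses another quantity: "the dosage of systemic glucocorticoids during the hospitalization of patients with AECOPD with TCM is 187.6 ± 31.1 mg", against 256.7 ± 32.9 mg with western medicine. No CAT condition is attached. The Introduction and Discussion likewise speak only of dosage or its reduction.

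Other sections bear on who can reach the milestone:
- Section 2.3 admits GOLD 3 or 4 patients who "have symptomatic COPD (CAT scores ≥ 10" or more.
- Section 2.6 starts methylprednisolone at 40 mg a day, lets it be reduced or switched to oral, and says "the longest course of treatment cannot exceed 14 days".
- Sections 2.7 and 2.14 put the stay at about 7 to 14 days, with CAT and dose recorded daily.
- Section 2.8 lists eight discharge criteria, the first being "Clinicians believe that patients can adapt to home medical care". None mentions CAT.
- Section 2.9 lists CAT, mMRC and 6MWD for the weekly calls after discharge, and no steroid dose.
- Section 2.16 plans intention-to-treat and per-protocol analyses, with a t test or a Wilcoxon rank-sum test.

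**The concern.** A dose at which CAT has improved by 50% exists only once CAT has improved by 50%. A patient sent home at 45% has received steroid but has no value on this outcome. Both named tests need a number for each patient. The intention-to-treat sentence settles which arm a patient counts in, but not what dose a non-reacher contributes.

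If non-reachers simply have no value, the comparison is between those who responded on each arm. Response comes after randomisation and may be changed by the granule, so the two sets of reachers need not be comparable. A granule that brings slow patients to the milestone late adds high-dose patients to its own arm and can look worse. One that stops slow patients from recovering removes its high-dose patients and can look steroid-sparing.

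This is more than a detail left to an analysis plan. It decides whether the primary variable exists for each randomised patient, and Section 2.5 rests on a variable that does.

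**Working it through.** **Planned effect.** From Section 2.5, 256.7 - 187.6 = 69.1 mg. At 40 mg a day this is 69.1/40 = 1.73 days (6.42 v 4.69 days). These are in-hospital doses without a CAT condition.

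**Can a patient miss the milestone?** Yes. Discharge needs no CAT change, the stay is limited, and no later dose is listed for collection. A patient admitted with CAT 10 to 19 must end at or below 5 to 9.5, under the entry level of 10.

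**Assumptions for the illustrations** (none is in the documents except 40 mg and 14 days): a constant 40 mg a day until the milestone and none after it. For the all-patient figures, non-reachers count as 14 × 40 = 560 mg.

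**Example 1, per 100 patients in each arm.** Arm 1: 50 reach at day 6 (240 mg), 20 at day 11 (440 mg), 30 never. Arm 2: 50 reach at day 6, 50 never.
- Reachers only: (50×240 + 20×440)/70 = 20,800/70 = 297.1 mg v 240 mg, so +57.1 mg against arm 1, although 70 v 50 patients responded.
- All patients: (20,800 + 30×560)/100 = 376 mg v (12,000 + 50×560)/100 = 400 mg, so -24 mg in favour of arm 1.
- If non-reachers receive X mg, the all-patient difference is 0.20 × (440 - X). It favours arm 1 only when X exceeds 440 mg; at X = 280 mg (7 days) it is +32 mg. Dose alone therefore cannot show benefit without the response rate beside it.

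**Example 2, a range.** Let p be the share who reach early (day e), h the share of the rest who reach late on TCM (day d), and let none of the rest reach on placebo. Then:
- TCM reachers: 40 × [p·e + (1-p)·h·d] / [p + (1-p)·h]
- TCM all patients: 40 × {p·e + (1-p)·[h·d + (1-h)·14]}

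With p = 0.6, e = 5 in both arms, h = 0.5 and d = 11: TCM reachers 40×(3 + 2.2)/0.8 = 260 mg v 40×5 = 200 mg on placebo. All patients: 40×(3 + 5) = 320 mg v 40×(3 + 5.6) = 344 mg.

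| Assumed pattern | Reach, placebo/TCM | Reachers only, TCM - placebo | All patients, TCM - placebo |
|---|---|---|---|
| Early day 5 in both arms, late day 11 | 80%/90% | +26.7 mg | -12.0 mg |
| Same | 60%/80% | +60 mg | -24 mg |
| Early half a day faster on TCM | 60%/80% | +45 mg | -36 mg |
| Planned gain (day 6.4 to 4.7), late day 12 | 90%/95% | -52.6 mg | -65.2 mg |
| Same | 80%/90% | -35.6 mg | -62.4 mg |
| Same | 60%/80% | +5.0 mg | -56.8 mg |
| All patients faster alike (lognormal, median 10 to 8 days) | 71%/82% | -32.6 mg | -50.8 mg |

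**Simulation of Example 1** (87 per arm, reaching days normal with SD 1.5). The reachers-only t test is significant against arm 1 in about 90% of trials. If all reachers in arm 1 are also one day faster, this falls to 12%; at the planned 1.73 days it is 0.2%. The harm in that last case is lost power: 7% among reachers only, against 88% when all patients are ranked with non-reachers worst. Those two powers are not like for like, since the ranking also counts response.

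**The case against.** The strongest reply is that the article never declares a reachers-only analysis. A reader might infer one from the statement that the efficacy analysis "analyzes only the completed cases". The text does not support that: the sentence removes patients with insufficient compliance, and a compliant patient discharged short of 50% is a completed case. An intention-to-treat analysis is planned as well. This stands. The reachers-only comparison is what the outcome definition leaves, and Section 2.16 does not prescribe it.

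A reader might also infer that non-reachers will be common. No section gives a reach rate, and the CAT 10 to 19 argument covers only the low end of eligibility. Non-reaching is possible; its frequency is unknown.

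The 90% figure should not be read as the expected error. It assumes that ordinary responders gain nothing and that the dose stays constant, although Sections 2.6 and 2.14 let it change. It drops sharply once reachers are faster on the granule.

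Nor do the documents show that lost non-reachers would leave too few patients. With the pooled SD √[(31.1² + 32.9²)/2] = 32.0, the formula in Section 2.5 gives 7.85 × 32.0² × 2/69.1² ≈ 3.4, so 4 per arm. The stated 87 does not follow from those inputs, which is a separate matter.

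Finally, a full analysis plan might assign values. It would still have to settle which of the two printed outcomes is primary.

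**Conclusion.** The point holds as a flaw in the outcome definition. Sections 2.1 and 2.10 define a dose that some patients may not have, Section 2.5 uses one that all have, and nothing printed bridges them. The definition also leaves open whether the dose is cumulative or the daily dose at the milestone.

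The size cannot be fixed from the documents. Under assumed reach rates the consequence runs from dilution (-52.6 v -65.2 mg with few failures, -32.6 v -50.8 mg when everyone speeds up alike) to a changed sign (+60 v -24 mg when the gain lies mainly in late reachers). The all-patient figures assume that non-reachers receive the full 560 mg. Reversal is possible but not shown to be likely. Because the gap sits in the primary outcome, it should be closed before anyone sees results by arm.

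**What to change.** Reconcile Sections 2.1 and 2.10 with Section 2.5, and define in Section 2.10 one primary value that exists for every randomised patient. One option is the cumulative methylprednisolone-equivalent dose actually received over a fixed window from randomisation, such as 14 days, the plan's own maximum course. Analyse it by intention to treat on all randomised patients. Report beside it the proportion in each arm reaching 50% CAT improvement, so that a lower dose is not read as benefit without symptom response.

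If the milestone version is kept, make it secondary and state how non-reachers are handled, for example by worst rank as a sensitivity analysis. Do not present a reachers-only comparison as the efficacy result. Worst rank is less suited to the primary analysis because it puts CAT response ahead of dose: a patient given 200 mg and discharged at 45% ranks below one given 560 mg who reached 50%. It can also penalise earlier discharge. With identical CAT courses but earlier discharge on the granule, it called the granule significantly worse in about 14 to 17% of simulated trials.

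The cost is a few sentences. In-hospital CAT and dose are already recorded daily. The primary outcome no longer has the CAT milestone built in, and patients discharged before the window ends need a stated rule for counting dose after discharge, which the follow-up calls would have to record.
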